If the intervention does not lead to a deterioration in health utility, cost analysis will estimate cost differentials between the intervention and control groups using an approach similar to that applied for the utility dimensions. If the initial steps of the analysis do not demonstrate clear dominance of one care alternative over the other (i.e., neither intervention nor control prevails), cost-effectiveness analysis will be conducted, computing an incremental cost-effectiveness ratio (ICER). Analysis is conducted from the perspective of the SHI community, with the time horizon covering at least the study observation period. To address statistical uncertainty, stochastic sensitivity analyses will be performed using Monte Carlo simulations. These simulations generate empirical distributions of the ICER by simulating utility and cost indices 10,000 times. This approach provides an ICER distribution that can be used to estimate the probability of the intervention meeting prespecified cost-effectiveness thresholds, similar to methods described in Gillespie et al.^
48
^

ICERs will be calculated for all five utility dimensions to provide a comprehensive basis for healthcare decision-making. However, given the recognized importance of the EQ-5D index in health economic evaluations, recommendations for implementing the intervention into standard care will be primarily based on its cost-effectiveness analysis. The Monte Carlo simulations generate empirical distributions for both the utility (denominator) and cost (numerator) components of the ICERs based on 10,000 simulations of the overall cost and utilities change associated with the intervention through the observed period *T*_0_–*T*_4_. The nuisance parameters used for this are estimated by the earlier-mentioned regression models. For instance, the ICER in the trajectory *s* is:

$${\mathrm{ICER}}_{s}=\frac{\Delta u_{0-4,s,\mathrm{IG}}-\Delta u_{0-4,s,\mathrm{CG}}}{\Delta c_{0-4,s,\mathrm{IG}}-\Delta c_{0-4,s,\mathrm{CG}}},$$

with

$\Delta \mu_{0–4,s,\mathrm{IG}}$
: average utility differential between *T_0_* and *T_4_* for intervention group in trajectory *s*,
$\Delta \mu_{0–4,s,\mathrm{CG}}$
: average utility differential between *T_0_* and *T_4_* for control group in trajectory *s*,
$Dc_{0–4,s,\mathrm{IG}}$
: average cost differential between *T_0_* and *T_4_* for intervention group in trajectory *s*,
$Dc_{0–4,s,\mathrm{CG}}$

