: average cost differential between *T_0_* and *T_4_* for control group in trajectory *s*.

This approach generates a non-parametric distribution for the ICER, which can be compared directly to predefined cost-effectiveness thresholds and provide a recommendation, if the implementation of the intervention is given some willingness to pay.

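### The displayed ICER formula is the reciprocal of the ICER the text defines, so applying it as printed makes the planned direct comparison with cost-per-utility thresholds uninformative

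*Protocol article*

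**What the plan says.** All of this is in the protocol article, Health economic evaluation, Statistical analysis, unless another section is named.

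- **Definition in words.** The article calls the quantity an incremental cost-effectiveness ratio and says the simulations "generate empirical distributions for both the utility (denominator) and cost (numerator) components of the ICERs". Cost is on top and utility below.
- **Definition in symbols.** The formula for trajectory s, offered as an example shortly afterwards, is in plain notation `ICER_s = (Δu_IG − Δu_CG) / (Δc_IG − Δc_CG)`, with all changes taken from T0 to T4. Utility is on top and cost below.
- **Symbol list.** The terms under the formula are defined in the order in which they are printed: first the mean utility change in each arm, then the mean cost change in each arm.
- **Use.** The distribution comes from "simulating utility and cost indices 10,000 times". It serves to "estimate the probability of the intervention meeting prespecified cost-effectiveness thresholds", and the section closes by calling it a distribution "which can be compared directly to predefined cost-effectiveness thresholds", with a recommendation that depends on willingness to pay.
- **Weight.** ICERs are planned for all five utility dimensions, and the recommendation on adoption into standard care rests mainly on the one for the EQ-5D index. Under Aims and objectives, a cost increase that is acceptable against such thresholds is one of three alternative conditions that would justify implementation.

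**The concern.** The two definitions cannot both hold. The words describe euros per unit of utility, where a lower value is better if both differences are positive. The formula gives units of utility per euro, where a higher value is better. The scale and the direction of preference both change.

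The thresholds and the willingness to pay belong to the first scale. The article does not say that the simulated ratio is inverted before the comparison, and it does not define a threshold in utility per euro. An analyst who programs the displayed formula and then makes the described comparison would set a very small number against a threshold in the thousands of euros. The resulting probability of meeting the threshold would not reflect value for money. At stake is the probability statement behind the implementation recommendation. The primary endpoint, sample size, randomization and data collection are not affected.

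**Working it through.** The article gives no ICER, threshold, expected cost difference or expected utility difference, so there is no figure to reproduce. The check has two parts: a reading of the text, and an illustration with assumed inputs.

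**1. Which quantity is on top?** By the sentence in words, cost is the numerator and utility the denominator. By the formula and its symbol list, the utility change is the numerator and the cost change the denominator. The list matches the printed order and the fraction is intact, so neither mislabelled symbols nor a damaged extraction explains the conflict.

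**2. Single values (all inputs assumed).** Let Δu and Δc be the differences, intervention minus control.

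| Δu | Δc (EUR) | As in the words, Δc/Δu (EUR per unit) | As printed, Δu/Δc (units per EUR) |
|---|---|---|---|
| 0.01 | 200 | 200/0.01 = 20,000 | 0.01/200 = 0.00005 |
| 0.02 | 300 | 300/0.02 = 15,000 | 0.02/300 = 0.0000667 |
| 0.005 | 1,000 | 1,000/0.005 = 200,000 | 0.005/1,000 = 0.000005 |

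**3. Simulated probabilities (all inputs assumed).** Each case used 10,000 independent normal draws, with SD 0.01 for Δu and SD EUR 300 for Δc. The thresholds were assumed to be EUR 10,000, 20,000 and 50,000 per unit of utility. Entries are the share of draws at or below each threshold, in that order.

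| Assumed means | Printed ratio | Ratio as in the words |
|---|---|---|
| 0.02, EUR 300 | 1.00, 1.00, 1.00 | 0.40, 0.63, 0.91 |
| 0.02, EUR 1,000 | 1.00, 1.00, 1.00 | 0.02, 0.07, 0.52 |
| 0.005, EUR 1,000 | 1.00, 1.00, 1.00 | 0.31, 0.32, 0.41 |

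The middle column follows from the units. With Δu = 0.02, the printed ratio exceeds 10,000 only if Δc lies between zero and 0.02/10,000 = EUR 0.000002. The printed ratio therefore cannot separate good value from poor value against such a threshold, whereas the ratio in words responds to both the threshold and the costs.

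The last row shows a different difficulty. About 31% of its draws have Δu below zero (Φ(−0.005/0.01) = Φ(−0.5) = 0.31), and a negative ratio then counts as meeting the threshold. At EUR 20,000 the share with positive net monetary benefit (threshold × Δu − Δc) is only 0.007, against 0.32 for the ratio. That concerns ratios whose components change sign. It is separate from the inversion, and swapping the fraction does not resolve it.

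**4. Comparison with a reciprocal threshold.** For EUR 20,000 per unit the reciprocal is 1/20,000 = 0.00005 units per euro. The example of EUR 200 and 0.01 falls exactly on it, so the printed ratio can be used this way when both differences are positive. In the EUR 1,000 case with Δu = 0.02, where cost draws are almost never negative, the share at or above the reciprocal was 0.048, against 0.049 with positive net monetary benefit. In the EUR 300 case, where some cost draws are negative, the shares were 0.45 and 0.61.

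**The case against.** The strongest reply is that the plan in words is already right. The article names the ratio correctly, states which component goes where, and shows the formula only as an example. The notation around the equations varies elsewhere too (u and μ, Δc and Dc). Some of that may come from text extraction, but it also fits a typesetting slip better than a wrong method. No code is shown, and an analyst who saw an ICER of about 0.00005 beside a threshold in euros would probably notice. This stands: the document cannot show that the inversion reached the analysis, and it lowers the severity.

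Two stronger readings are tempting, and the document supports neither.

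- **A reader might infer that no comparison with a threshold could be meaningful.** That goes too far. When both differences are positive, the printed ratio can be set against the reciprocal of the threshold. What fails is the direct comparison that the article describes.
- **A reader might infer that the formula would favour the intervention whatever the data, even if it were harmful and more expensive.** The stepwise procedure argues against this. Cost analysis follows only if health utility has not deteriorated, and the ICER is computed only if neither alternative is clearly dominant. A clearly harmful and costlier intervention should stop before the ICER.

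It is also fair to say that the simulated 100% restates the inversion through its units and does not measure harm to this trial.

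The reply does not remove the contradiction. The article prints an explicit formula that disagrees with its own text. This is an error in what is stated, not detail left to a fuller plan.

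**Conclusion.** The formula is wrong as written: it is the reciprocal of the ICER defined in the same section. Used as printed, the direct comparison with a cost-per-utility threshold would be uninformative, as with 0.00005 in place of EUR 20,000 per unit in the assumed example. This rests on reading the unstated thresholds as euros per unit of utility, which is the scale implied by the article's own definition of the ratio and its mention of willingness to pay. All effects, SDs and threshold values in the illustration are assumptions.

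The contradiction itself is certain; its effect on the eventual analysis is not, since correct code may already exist. The matter is confined to the health economic evaluation and can be corrected at any time before that analysis. It deserves correction because the EQ-5D ICER carries most of the weight in the implementation recommendation, but it does not threaten the validity of the trial.

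**What to change.** Replace the displayed formula with `ICER_s = (Δc_IG − Δc_CG) / (Δu_IG − Δu_CG)`, put the symbol list in the same order, and use one symbol each for utility and cost throughout. Confirm that the simulation code uses this orientation for all five utility dimensions. The cost is one corrected formula and a short code check; data collection, sample size and trial conduct are unchanged.

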#### Statistical analysis

The health economic evaluation follows a three-step procedure previously recommended for health economic analyses in Germany.^
47
^ Cost analysis employs a *difference-in-differences* (DiD) approach to compare trends in individual healthcare cost estimates between the intervention group and the control group, incorporating both direct and indirect costs.

In the first step, utility analysis is conducted using the DiD method to compare changes across the five utility dimensions at the individual level. Utility differentials are calculated between the four survey periods and subsequently compared between the IG and CG using hypothesis testing. For instance, for a patient *i*, the first differences in some utility index between periods 0 and 1 are

$$\Delta u_{i,1}:=u_{i,1}-u_{i,0},$$

With *μ*_i,0_ being the observation for the respective utility index at *T*_0_ for patient *i*. We check the null hypothesis that the utility differentials are not associated with whether the patients belong to the IG or the CG, that is, for

$$\Delta u_{i,t}=\delta I+\beta \prime x_{i},$$

we check

$$H_{0}:\delta =0.$$

Here, *I* is a binary variable that takes the value 1 for patients of the IG and 0 for those in the CG. **
*x*
**_i_

$x_{i}$
 is a vector of sociodemographic predictors. Those are included to avoid a potential bias in the test results because of heterogeneities between the two study groups. If the null hypothesis of interest can be rejected, the intervention is associated with different utilities than the standard treatment. The Greeks are parameters estimated based on the data via ordinary least squares.

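### The ICER simulation takes its inputs from separate cost and utility regressions, with no stated step that carries their covariance into the draws, and its result is labelled non-parametric

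*Protocol article*

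**What the plan says.** All of this is in the Statistical analysis section of the health economic evaluation in the protocol article.

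- **Utility.** For each utility index, the patient's change is regressed on trial arm and sociodemographic covariates. "The Greeks are parameters estimated based on the data via ordinary least squares".
- **Cost.** This is a later step, taken only if utility has not worsened: "cost analysis will estimate cost differentials between the intervention and control groups using an approach similar to that applied for the utility dimensions".
- **Simulation.** If neither alternative dominates, an ICER is computed and its uncertainty simulated. "These simulations generate empirical distributions of the ICER by simulating utility and cost indices 10,000 times". On the inputs: "The nuisance parameters used for this are estimated by the earlier-mentioned regression models". On the output: "The Monte Carlo simulations generate empirical distributions for both the utility (denominator) and cost (numerator) components of the ICERs".
- **Use.** The distribution serves to "estimate the probability of the intervention meeting prespecified cost-effectiveness thresholds". Advice on adoption into standard care is to rest mainly on the EQ-5D index version.
- **Label.** "This approach generates a non-parametric distribution for the ICER".

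The article gives no threshold value, no standard deviation for cost or utility change, and no cost-utility correlation.

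**The concern.** Cost and EQ-5D are collected from the same patients at the same time points (Tables 4 and 10), so their increments cannot be assumed uncorrelated. The probability of cost-effectiveness depends on the variance of net benefit, which contains a covariance term. A single-outcome regression returns an arm effect and its variance for that outcome only. Two such regressions, taken as they stand, leave the covariance term empty. A programmer who followed the text literally could draw the two increments independently without noticing that a choice had been made.

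The label is a second matter. Draws generated from regression coefficients and variances need an assumed distributional form. Repeating them 10,000 times does not remove that assumption. The label therefore suggests a freedom from assumptions, for instance about skewed costs, that the described method does not have.

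**Working it through.** The plan states no figure on this point to reproduce, so the check asks what the regressions can supply and how much the covariance could matter.

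**1. Quantity at issue.** Write dE and dC for the incremental utility and cost, seE and seC for their standard errors, rho for the correlation between the two estimated increments, and L for the threshold. Under a normal approximation:

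P(cost-effective) = Phi[(L·dE − dC) / sqrt(L²·seE² + seC² − 2·L·rho·seE·seC)]

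Independent draws correspond to rho = 0.

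**2. Inputs.** From the Sample size section: 264 evaluable patients, so 132 per arm, and a design effect of 1 + (6 − 1) × 0.05 = 1.25. Assumed, because the article gives no values: SD of EQ-5D change 0.20, SD of cost change EUR 6,000, and the increments and thresholds in the table. Then sqrt(1.25 × 2/132) = 0.1376, so seE = 0.20 × 0.1376 = 0.0275 and seC = 6,000 × 0.1376 = EUR 826.

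**3. Results.**

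| dE | dC (EUR) | L (EUR) | rho = −0.6 | rho = −0.4 | rho = 0 | rho = +0.4 |
|---|---|---|---|---|---|---|
| 0.05 | 300 | 30,000 | 0.792 | 0.807 | 0.848 | 0.908 |
| 0.03 | 300 | 30,000 | 0.658 | 0.668 | 0.696 | 0.746 |
| 0.01 | 600 | 20,000 | 0.373 | 0.365 | 0.343 | 0.306 |
| 0.02 | 600 | 30,000 | 0.500 | 0.500 | 0.500 | 0.500 |

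First row in full: net benefit is 30,000 × 0.05 − 300 = 1,200, and L·seE = 826, equal to seC. At rho = 0 the standard error is 826 × sqrt(2) = 1,168, z = 1.03 and P = 0.848. At rho = −0.6 it is 826 × sqrt(3.2) = 1,477, z = 0.81 and P = 0.792. At rho = +0.4 it is 826 × sqrt(1.2) = 905, z = 1.33 and P = 0.908. Assuming rho = 0 would therefore be 5.6 points too high in one case and 6.0 points too low in the other. In the third row net benefit is negative (20,000 × 0.01 − 600 = −400) and the direction reverses. In the fourth it is zero (30,000 × 0.02 − 600) and rho has no effect.

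Wherever L × SD of utility change equals SD of cost change, as at L = 30,000 here, a given rho has its largest relative effect on the standard error. The upper figures are therefore close to a worst case for that rho.

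**4. Can the separate fits supply the covariance?** Yes, with one further step. If both regressions use the same covariates, the covariance of the two arm effects is the cross-equation residual covariance multiplied by the arm element of the inverse of X′X. In a simulated sample of 264 patients with a true residual correlation of −0.4, equation-by-equation least squares and seemingly unrelated regression (SUR) gave identical arm effects, and the residual correlation was recovered as −0.33. With that sample's covariance, ignoring clustering, and with dE = 0.03, dC = EUR 300 and L = EUR 30,000, joint draws gave P = 0.682 and independent draws 0.709. The gap is thus the missing covariance step. Fitting the outcomes separately does no harm in itself.

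**The case against.** A reader might infer that the plan ignores the cost-utility correlation and will therefore report a wrong probability. The documents do not support that. Nowhere does the article say that the draws are independent. Its ICER formula indexes the cost and utility differentials by the same simulated trajectory, which is compatible with joint draws though it does not prove them. As step 4 shows, it would also be wrong to say that separate least-squares fits cannot yield a covariance. An article condenses a fuller protocol and analysis plan, and this section points to a published method that is not at hand. The missing step may be written down elsewhere.

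Every magnitude input is assumed, and the sign of the correlation is unknown. The simulations are described as stochastic sensitivity analyses and are reached only if neither alternative dominates. The simulated quantities are arm averages, so skew in individual costs matters less than it would for single patients, and no effect of skew has been quantified here. The label might also be read loosely, as saying only that the simulated values are summarized without fitting a curve to them.

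These points limit the claim without removing it. The article goes beyond silence: it names the source of the simulation's parameters, and that source as described holds no covariance. The looser reading of the label does not change how the draws are produced.

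**Conclusion.** The concern holds as a gap in a method that is otherwise spelled out. The simulation is parameterized from single-outcome regressions, and no joint model, cross-equation covariance or paired resampling is described. If it is run from those parameters alone, the probability of meeting a threshold can be misstated by 0 to about 6 percentage points for correlations between −0.6 and +0.4 under the assumed inputs. Neither size nor direction can be derived from the documents. The shift is modest, but it falls on the probability that informs the recommendation on routine care and could matter near a decision cut-off. The non-parametric label is inaccurate for draws from fitted parameters, whether or not they are joint. This is an inexpensive improvement that should be made. It does not show that the planned analysis is invalid.

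**What to change.** Preferred: replace the parametric draws with a bootstrap that resamples whole clusters within arm and study center, keeps each patient's cost and utility as a pair, and recomputes both increments in every replicate. This carries the correlation and the shape of the cost distribution, respects clustering (the regression as displayed has no cluster term, although the sample size assumes an ICC of 0.05), and makes the label true. With 44 clusters over two arms and three centers there are on average 44/6, or about 7, clusters per stratum, so the code should include a small-stratum correction.

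Alternative: keep the simulation, draw the cost and utility increments jointly using the cross-equation covariance (SUR or a bivariate model) with cluster-robust variance, and delete the word non-parametric.

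Either way, the cost is a little more analysis code and about two sentences of text. No further data are needed. The stated uncertainty may become somewhat wider.

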#### Outcomes

##### Data collection

Participating GP practices, pharmacies, and patients serve as data sources. GP practices document relevant data to characterize the patient collective upon inclusion in the study, and GP practices and pharmacies document all study-related patient contacts during the follow-up in the intervention group. All study endpoints listed in Tables 4 to 9 are collected by trained study personnel via patient interviews. The follow-up period is 12 months, with data collection taking place at five points in time:

Data collection for T_0_ is at randomization.T_1_, T_2_, T_3_, and T_4_ are defined as 3, 6, 9, and 12 months after the pharmacy consultation in each arm, respectively.In case the pharmacy consultation does not take place within 3 months after randomization (protocol deviation), T_1_, T_2_, T_3_, and T_4_ are defined as 6, 9, 12, and 15 months after randomization.

**Table 5. table5-20420986251400042:** Primary outcome—PSA-PIM deprescribing.

No.	Source population	Parameter	Time of measurement*
Impact on DBI response			
Primary outcome	All study participants	Number of patients in source population with a reduction in the DBI (including all PSA-PIMs) of ⩾0.15	T_2_ vs T_0_

The outcome is the rate of parameter/source population in the intervention versus the control arm.

* Data collection for T_0_ is at randomization. T_1_, T_2_, T_3_, and T_4_ are defined as 3, 6, 9, and 12 months after the pharmacy consultation in each arm, respectively. In case the pharmacy consultation does not take place within 3 months after randomization (protocol deviation), T_1_, T_2_, T_3_, and T_4_ are defined as 6, 9, 12, and 15 months after randomization.

DBI, Drug Burden Index; PSA-PIM, psychotropic, sedating, and anticholinergic potentially inappropriate medication.

**Table 6. table6-20420986251400042:** Secondary outcomes (SO)—PSA-PIM deprescribing and use.

No.	Source population	Parameter	Time of measurement*
Sustained and stratified impact on DBI response			
SO1	All study participants	Number of patients in source population with a reduction in the DBI (including all PSA-PIMs) of ⩾0.15	• T_4_ vs T_0_
SO2	Study participants with chronic pain psychotropics at baseline	Number of patients in source population with a reduction in the DBI (including chronic pain psychotropics only) of ⩾0.15	• T_2_ vs T_0_ • T_4_ vs T_0_

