HEO3	Quality of life (EQ-VAS)	- Provision of remedies and aids - Outpatient care/rehabilitation	T_0_, T_1_, T_2_, T_3_, T_4_
HEO4	Falls (Patient Diary)	- Resources GP practice/pharmacy (personnel, infrastructure, and material)	T_1_, T_2_, T_3_, T_4_
HEO5	Cognition (Verbal Fluency Test Score)		T_0_, T_2_, T_4_

* Data collection for T_0_ is at randomization. T_1_, T_2_, T_3_, and T_4_ are defined as 3, 6, 9, and 12 months after the pharmacy consultation in each arm, respectively. In case the pharmacy consultation does not take place within 3 months after randomization (protocol deviation), T_1_, T_2_, T_3_, and T_4_ are defined as 6, 9, 12, and 15 months after randomization.

EQ-5D-5L, EuroQol 5-Dimension 5-Level questionnaire; EQ-VAS, EuroQol Visual Analogue Scale; HEO, health economic outcomes.

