#### Data collection and outcome measures

Table 10 outlines health economic outcomes (HEO1 to HEO5), including the cost and benefit endpoints considered in the analysis.

*Health-related utility*: Health-related utility is measured across five dimensions:

*DBI*: Calculated based on patient interviews.*EQ-5D index*: Measures health-related quality of life using data from the EQ-5D-5L questionnaire, deriving a summary statistics from time-tradeoff analysis.^37,42^*EQ-VAS*: Measures health-related quality of life using data from the EQ-5D-5L questionnaire based on a visual analog scale.*Incidence of falls*: Captured through patient diaries.Cognition index: Assessed via a VFT.

*Cost analysis*: Intervention costs are categorized into *direct* and *indirect* costs:

*Direct costs* are estimated based on documented expenses for informational materials and the time invested by GPs, nursing staff, and pharmacists related to the intervention. Time units are multiplied by corresponding cost units, derived from current reports and published unit costs.*Indirect costs* are assessed by collecting data on healthcare utilization over 3-month periods for both study groups. This includes physician visits, outpatient or inpatient hospital care, and physical or occupational therapies. Data is gathered using a validated questionnaire for Germany.^39,40^ Healthcare utilization is then multiplied by cost units, as done for direct cost estimation.

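### The ICER terms are defined as T4-minus-T0 changes: for the EQ-5D index this is not a QALY, for costs read literally it is not a cost over the horizon, and for falls it cannot be formed

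*Protocol article*

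**What the plan says.** All references are to the protocol article; no analysis plan is at hand.

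- **What a differential is.** Under Health economic evaluation, Statistical analysis, the worked example for "the first differences in some utility index between periods 0 and 1 are" the T1 value minus the T0 value.
- **Step 1, utilities.** There, "utility analysis is conducted using the DiD method to compare changes across the five utility dimensions at the individual level". The testing rule is: "Utility differentials are calculated between the four survey periods and subsequently compared between the IG and CG using hypothesis testing". Costs follow a similar approach, and the section says that direct and indirect costs are both incorporated.
- **ICER terms.** For utility, "average utility differential between *T_0_* and *T_4_* for intervention group in trajectory" s, with a matching control-arm term. For cost, "average cost differential between *T_0_* and *T_4_* for control group in trajectory" s, with a matching intervention-arm term. The lead-in describes simulating an overall change over T0 to T4.
- **Use.** ICERs are promised for all five utility dimensions. The recommendation rests mainly on the EQ-5D index, and the ICER distribution is compared with predefined thresholds. The time horizon is at least the observation period.
- **Cost data.** Under Data collection and outcome measures, indirect costs come from "collecting data on healthcare utilization over 3-month periods for both study groups". Direct costs are materials and staff time.
- **Schedule.** Quality of life and utilization are collected at T0 to T4. In Table 10, HEO4, "Falls (Patient Diary"), is listed at T1 to T4 only. T0 is at randomization, and T1 to T4 are counted from the pharmacy consultation.

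**The concern.** An ICER meant for a decision threshold needs health accrued and cost incurred over the same horizon. A T4-minus-T0 difference gives neither. For the EQ-5D index it gives the change in a level between two dates, so the timing of benefit or harm within the year has no influence. That matters here because the Introduction describes withdrawal symptoms and rebound, and the GP consultation component calls withdrawal symptoms usually temporary. The visits at which a temporary loss would show are the ones that the ICER does not use.

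For costs, each survey yields a 3-month amount. Subtracting the T0 amount from the T4 amount compares one quarter before the intervention with the last quarter of follow-up.

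At stake is the size, and possibly the sign, of the quantity on which the implementation recommendation mainly rests.

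**Working it through.** The plan states no figure to reproduce, so the check sets the definitions against the schedule and then illustrates the size.

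**1. Does adding up the period differentials help?** Five time points give four intervals. If each differential is taken against the preceding survey, their sum is

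(u1 - u0) + (u2 - u1) + (u3 - u2) + (u4 - u3) = u4 - u0.

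The intermediate values cancel. The same holds for costs. Only differences taken each time against T0 accumulate: the sum over t = 1 to 4 of (ct - c0) is c1 + c2 + c3 + c4 - 4c0. The printed T0-to-T4 term is not defined that way.

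**2. Utility.** The between-arm EQ-5D differences below are assumed, placed at 0, 3, 6, 9 and 12 months. With a zero difference at T0, the trapezoid rule gives area = 0.25 × (d1 + d2 + d3 + d4/2).

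| Assumed difference at T0, T1, T2, T3, T4 | T4 - T0 | QALY |
|---|---|---|
| 0, 0.0125, 0.025, 0.0375, 0.05 | 0.05 | 0.25 × (0.075 + 0.025) = 0.025 |
| 0, -0.03, -0.02, -0.01, 0 | 0 | 0.25 × (-0.06) = -0.015 |
| 0, 0.04, 0.04, 0.04, 0.04 | 0.04 | 0.25 × (0.12 + 0.02) = 0.035 |
| 0, -0.04, -0.02, 0, 0.04 | 0.04 | 0.25 × (-0.06 + 0.02) = -0.010 |
| 0, 0.04, 0.04, 0.02, 0 | 0 | 0.25 × 0.10 = 0.025 |

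The third and fourth rows have the same T4-minus-T0 value and QALYs of opposite sign.

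**3. Dates.** Table 4 puts T0 one month before the consultation, which makes the first interval 4 months. The recovering dip in the second row is then (4/12) × (-0.015) + 0.25 × (-0.025 - 0.015 - 0.005) = -0.005 - 0.01125 = -0.01625. Under the fallback for a late consultation, T1 is 6 months after randomization and the result is -0.0075 - 0.01125 = -0.01875. Actual dates are therefore needed.

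**4. Cost.** The between-arm differences in euro per 3-month window are assumed, with zero difference at T0.

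| Assumed difference at T1, T2, T3, T4 | T4 - T0 | Sum of four windows |
|---|---|---|
| -50, -50, -50, -50 | -50 | -200 |
| +100, +50, 0, -50 | -50 | +100 |

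The formula shows the same saving in both rows; the second is a net cost.

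**5. One-off delivery cost.** Table 4 places delivery between minus 1 month and plus 2 weeks. If each window looks back 3 months from its survey, T4 covers months 9 to 12 after the consultation. A delivery cost D belongs in full in a cost over the horizon, but the printed T4-minus-T0 term does not say at which time point D is counted.

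**6. Falls.** The differential needs a T0 value. Tables 9 and 10 list falls at T1 to T4 only, so the falls ICER cannot be formed as defined.

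**The case against.** The strongest defence is that the printed formula is shorthand. The lead-in speaks of an overall change through the observed period, the horizon is at least that period, and the nuisance parameters come from the period regressions. For costs this leaves room for a cumulative intention, so the two-quarter contrast is the literal reading and not a certain one. It does not rescue the utility term: no QALY or area under the curve is mentioned, and first differences sum back to u4 - u0. Nor is this a detail left to an unseen plan, since the article prints the definition.

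Several stronger readings are tempting but not supported.

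- **The intervention's own cost is left out.** The section says that direct costs are incorporated, and Table 10 lists practice and pharmacy resources. What is missing is where they enter the formula.
- **A temporary loss goes unseen altogether.** Step 1 tests differentials between surveys, the cost analysis is conditional on no deterioration in utility, and EQ-5D is a secondary outcome at T0 to T4 (SO20). The loss is absent from the ICER term only.
- **HEO1 is undefined at T0.** The outcome-measures section names the DBI itself, and Table 10 lists it at T0. The text should say whether responder status or DBI change is meant.
- **The control consultation is costed at zero.** A reader might infer this from "GP practices and pharmacies document all study-related patient contacts during the follow-up in the intervention group". That sentence concerns who documents contacts; it does not set a cost.
- **The fees of €180 and €120 show how far delivery cost would be overstated.** They compensate time, effort and documentation, and control GP practices receive theirs although the only control component is a pharmacy review. They are no measure of delivery cost.

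**Conclusion.** The point holds for the ICER definition. The EQ-5D term is an index change and not a QALY, and T1 to T3 do not enter it. The cost term, read literally, contrasts two 3-month windows and conflicts with the plan's own horizon. The falls term has no T0 value.

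In the assumed trajectories, one and the same T4-minus-T0 gain of 0.04 corresponds to -0.010 or 0.035 QALY, and one and the same apparent saving of €50 corresponds to a saving of €200 or a cost of €100. These figures show what the definition permits; they do not forecast this trial. They rest on the assumed trajectories, a zero difference at T0, and the 3-month grid except where varied.

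The consequence is greatest for the EQ-5D ICER, because the recommendation mainly rests on it. A threshold expressed per QALY could not be applied to the printed quantity; the article gives neither the value nor the unit of its thresholds. The falls problem is real but secondary. This should be corrected before the economic analysis is run.

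**What to change.** State the ICER terms as follows:

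- **Effect:** QALYs as the area under the EQ-5D index from T0 to T4, using actual assessment dates (T0 at randomization, T1 to T4 from the consultation or under the fallback rule), adjusted for T0 utility.
- **Cost:** the sum of the follow-up utilization windows plus direct delivery cost, costed on the same basis in both arms, adjusted for T0 cost. Say how the interval between randomization and the first window is handled: about one month by Table 4, and three months under the fallback rule if windows look back 3 months.
- **Falls:** rates over follow-up from the diary counts, with person-time and no baseline difference.
- **HEO1:** the responder proportion, or the DBI change if the continuous index is meant.

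The step-1 tests can stay. The utility, utilization and falls data are already scheduled. The change costs analysis wording and minor additional analysis work, plus a stated basis for costing delivery in the control arm.
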